**ABSTRACT**

The objective of this study will be to evaluate the efficacy of regular cleaning of the oropharynx on the incidence of symptoms associated with flu and colds. A total of 150 individuals will be randomized to one of the two experimental regimens and followed for a period of 90 days. The experimental regimes include: control, using toothpaste and a soft toothbrush; and test: using dentifrice, soft toothbrush, and mouthwash for gargling containing cetylpyridinium chloride (CPC) (0.075%) and zinc in an alcohol-free solution. All products are commercially available and will be provided by the research team. Participants will be instructed to brush their teeth twice a day for two minutes. Those allocated to the test regime will gargle with 20 ml of the mouthwash after each brushing. At the initial visit, participants will receive the products and instructions for use, as well as a daily log questionnaire. Participants will be asked to send their daily records once a week, using a messaging application. The proportion of days without any of the evaluated symptoms will be used as the main outcome. In addition, soft and hard tissue exams will be performed at the initial consultation, after 30 and 90 days of follow-up. Possible adverse events will be collected throughout the study. The groups will be compared using the chi-square test and the significance level will be set at 95%.

**Key-words:** Influenza, Oropharynx, Cetylpyridinium

# **INTRODUCTION**

Respiratory infections of viral origin are responsible for high degrees of morbidity and mortality around the world. Among viral respiratory infections, those caused by the Influenza virus are one of the most common. Furthermore, its impact on health systems is of great importance (FRASER, TOMBE-MDEWA, KOHLI-LYNCH, *et al*., 2022).

Since the emergence of the COVID-19 pandemic, interest in viral respiratory infections has grown, and a series of studies have been performed to understand the role of different strategies that could mitigate the effects of viral respiratory infections. For both influenza and COVID-19 infections, vaccination has proven to be a preventive and damage limitation strategy with satisfactory degrees of efficiency, from individual and, mainly, collective aspects.

However, in addition to vaccination, different strategies have been proposed. Specifically in the case of the oral cavity, studies have been performed with different agents previously used with the aim of supporting oral hygiene and have been revisited in relation to their antiviral capacity (FERNANDEZ, GUEDES, LANGA, et al., 2022), with a view to determining possible/potential effects on viral respiratory infections, considering that the oropharynx is one of the affected spaces and a potential entry point for the infection. However, much of this literature comes from *in vitro* studies, and there is a gap in the literature regarding the clinical antiviral efficacy of these oral hygiene products.

Similarly to hand washing/hygiene, which has been considered an impactful measure in preventing the spread of viral infections, it is hypothesized that oral and oropharyngeal hygiene measures may also have such beneficial effects. Within this context, clinical trials that verify the clinical efficacy of these agents are necessary.

In this sense, mouthwash solutions have been studied in relation to their antiviral potential. When chlorhexidine-based solutions are evaluated, in a systematic review of the literature, it is observed that they may have an interesting virucidal effect on influenza viruses and even SARS-COV 2 (FERNANDEZ, GUEDES, LANGA, et al., 2022).

Other studies have been carried out and sought to evaluate the potential of solutions used locally in the mouth/oropharynx region in the context of viral infections. In an *in vitro* study, using two commercially available toothpastes and two mouthwash solutions, it was observed that rinsing with hydrogen peroxide, or with cetylpyridinium chloride, or using toothpastes with stannous fluoride had important antiviral effects (RAMJI, CIRCELLO, WINSTON, et al., 2022).

Cetylpyridinium chloride (CPC) is a quaternary ammonium compound, with high safety and widespread use as an adjunct to oral hygiene procedures. It has good adherence by patients, and its antibacterial effect on the oral microbiota is undisputed (LANGA, MUNIZ, COSTA, et al., 2021). Furthermore, recently, the literature has demonstrated that the addition of zinc (Zn) to mouthwashes containing CPC has demonstrated superior clinical effects when compared to mouthwashes containing only CPC (RÖSING, CAVAGNI, GAIO et al., 2017) or essential oils (LANGA, CAVAGNI, MUNIZ et al., 2021). However, its antiviral potential is still little tested, but it has potential and has been recommended as a pre-operative mouthwash for dental procedures (RETAMAL-VALDES, SOARES, STEWART, et al., 2017).

Based on these potentials and the need for clinical studies, in addition to the possible effect of the topical use of oral antiseptics to reduce viral infections, this study is justified, which aims to evaluate the effect of using a CCP+Zn solution in the form gargling when flu and cold symptoms occur. The hypothesis under study is that the local presence of CCP+Zn can reduce the occurrence of flu-like symptoms when compared to the absence of these active ingredients.

# **AIM**

The aim of this study will be to evaluate the efficacy of regular cleaning of the oropharynx, on the incidence and duration of symptoms associated with flu and colds, with the use of CCP+Zn gargling compared to the absence of gargling.

# **HYPOTHESIS**

The operational hypothesis is that there will be a significant reduction in symptoms associated with flu and colds after using the CCP+Zn-based product, compared to the experimental control regime.

# **METODOLOGY**

# **4.1. Experimental design and place of performance**

This is a phase III, randomized, controlled, parallel, single-center clinical trial to evaluate the efficacy of regular oropharyngeal cleaning on the incidence and duration of symptoms associated with cold and flu. The study will be carried out in the dental clinics of the Faculty of Dentistry of the Federal University of Pelotas (UFPel).

## **4.2. Study population**

One hundred and fifty (150) individuals, aged 18-70 years, will be included in this study.

### Sample size

The sample size of 150 individuals (75 per group) was based on internal data from the sponsor of this study. It was determined that 60 individuals per group are needed for 80% power for the occurrence of flu-like symptoms. Considering the nature of the study and the demand for daily questionnaire responses, an attrition rate of 25% is assumed over the course of the study.

- - 1. Inclusion criteria

Individuals must meet all the following criteria:

1. Sign this informed consent form (ICF) (Appendix A);

2. Men or women, aged between 18 and 70;

3. Good systemic general health as determined by study investigators;

4. Availability of 90 days to participate in the study;

- - 1. Exclusion criteria

During the study, the following exclusion criteria will be considered:

1. Be participating in any other clinical study;

2. Being pregnant or breastfeeding;

3. Present a history of allergies to oral hygiene products, personal hygiene products, or their ingredients;

4. Have mouth irritation or use oral anesthetic sprays;

5. Have diabetes;

6. Be undergoing extensive dental treatment or oral surgery during the study;

7. Present immunocompromised (HIV, AIDS, immunosuppressive drug therapy);

8. Use complete dentures;

9. Have carpal tunnel syndrome or arthritis in the hands.

10. Participant who substantially fails to follow the required protocols;

11. Participant who fails to attend scheduled appointments;

12. Participant who is treated, during the study period, with medications that may interfere with the parameters being analyzed in the study;

13. Participant who is treated by a medical or dental service, and this may interfere with the parameters being analyzed in the study;

14. Participant who develops serious adverse reactions. The investigator will immediately record the information on the Adverse Reactions Form (Appendix B);

15. The participant who chooses to end their participation in the study;

16. Participant reports being pregnant during the study.

- 1. **Tests products**

Participants will be randomized into one of the following experimental regimens and will receive products as follows:

Group control:

● Colgate Maximum Cavity Protection® Toothpaste.

● Commercially available soft toothbrush.

Test Group:

● Mouthwash containing 0.075% CCP and 0.28% zinc lactate, in an alcohol-free base, commercially available in Brazil.

● Colgate Maximum Cavity Protection® Toothpaste.

● Commercially available soft toothbrush.

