## **4.4. Experimental procedure**

### 4.4.1. Selection of participants

Research participants who sign the informed consent form and answer to the health questionnaire (Appendices A and C) will receive an intraoral clinical examination to identify whether they meet the inclusion and exclusion criteria. All individuals will receive an assessment of their soft and hard oral tissues, findings will be recorded on the Hard and Soft Buccal Tissue Form (Appendix D). The initial questionnaire will be recorded on the Initial Examination Form (Appendix E). The first 150 individuals who meet the inclusion criteria, sign the consent form and the health questionnaire will be included in the study. After initial assessments, all individuals will receive a questionnaire to record daily symptoms associated with the flu and cold (Appendix F). This form will be delivered in physical format, with the questionnaire for the 90 days of the study, to facilitate completion by the participant. Once a week, participants must send photographs of their daily records. This will be sent via a messaging application. Participants will be reimbursed amounts compatible with internet packages. The research team undertakes to download the records and store them on devices on external physical drives, not connected to the internet. Messages will be deleted immediately after downloads. Furthermore, confidentiality of participants' data will be ensured throughout data storage and other procedures of this study.

The selection of participants will be of convenience based on a verbal invitation at the different clinics of the Dentistry Faculty of Federal University of Pelotas. In addition, recruitment may include posts on social media, which explain the main objectives of the present study. Those who express interest in participating in the study will receive the consent form in two copies and, after reading and signing it, will be evaluated based on the following exams:

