## **4.7. Statistical analysis**

Chi-square test will be performed for gender data, and an independent t-test for the age variable, to test the hypothesis that the groups present balanced distribution of variables. The proportion of symptom-free days (i.e., none of the 10 symptoms were present) will be used for the primary outcome variable. Chi-square test will be used to compare the proportion of symptom-free days for the experimental groups. Analysis of variance can be used to compare groups. Significance level will be set at 95%.

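### Enrolling 75 per group leaves about 56, not the required 60, after the plan's own 25% attrition; power falls from 80% to about 77% if lost participants contribute no data

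*Combined protocol and SAP*

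**What the plan says.** Section 4.2.1 (Sample size) is the only sample-size justification in the plan. It gives three figures in turn.

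- Enrolment: "The sample size of 150 individuals (75 per group) was based on internal data from the sponsor of this study".
- Requirement: "It was determined that 60 individuals per group are needed for 80% power for the occurrence of flu-like symptoms".
- Expected loss: "an attrition rate of 25% is assumed over the course of the study". The reason given is the nature of the study and the burden of a daily questionnaire.

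The total of 150 is fixed elsewhere too. Section 4.2 repeats it. Section 4.4.1 says "The first 150 individuals who meet the inclusion criteria, sign the consent form and the health questionnaire will be included in the study". Section 4.4.3 numbers participants from 001 to 150. The Budget pays for 150 diary books, 150 internet reimbursements and 450 journeys (150 × 3 visits). Nothing provides for replacing participants who leave or for enrolling more than 150.

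The plan gives no effect size, event rate or standard deviation behind the 60.

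**The concern.** Attrition over the course of a study is a fraction of those enrolled. To finish with a required number, that number is divided by one minus the attrition rate. Multiplying it by one plus the rate applies the loss to the completers and gives too small a figure. The 75 in section 4.2.1 matches the multiplication exactly and does not match the division.

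At stake is whether the power claim survives the plan's own attrition assumption. If the trial shows no difference, readers will use the 80% to judge how informative that result is. The shortfall biases no estimate and does not alter the analysis.

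**Working it through.** **Inputs.** From section 4.2.1: 60 per group required, 80% power, 25% attrition, 75 per group enrolled. From section 4.7: a significance level given as 95%, read here as α = 0.05. Sidedness is not stated, so two-sided is assumed and one-sided is shown as a range. The effect size is not given.

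**Step 1: reproduce the plan's figure.** 60 × (1 + 0.25) = 75, an exact match. The plan does not state this formula; it is inferred from the match.

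**Step 2: inflate for a loss from those enrolled.** 60/(1 − 0.25) = 60/0.75 = 80 per group, 160 in total. Check: 80 × 0.75 = 60.

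**Step 3: what 75 per group leaves.** 75 × 0.75 = 56.25 per group, or 150 × 0.75 = 112.5 in total against 120 required. The shortfall is 3.75 per group, and 3.75/60 = 6.25%.

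**Step 4: the attrition that 75 per group does cover.** 1 − 60/75 = 20%.

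**Step 5: power at the retained size.** The effect is unknown, so calibrate it to give 80% power at 60 per group. With two-sided α = 0.05 this fixes the standardised distance at 1.960 + 0.842 = 2.802. At n per group,

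power = Φ(2.802 × √(n/60) − 1.960).

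At n = 56.25: √0.9375 = 0.9682; 2.802 × 0.9682 − 1.960 = 0.753; Φ(0.753) = 0.774.

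| Attrition from 75 | Left per group | Power, two-sided |
|---|---|---|
| 15% | 63.75 | 82.3% |
| 20% | 60 | 80.0% |
| 25% | 56.25 | 77.4% |
| 30% | 52.5 | 74.6% |

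**Step 6: sensitivity to the assumptions.**

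| Method | 56 per group | 56.25 per group |
|---|---|---|
| Normal approximation, two-sided | 77.2% | 77.4% |
| Normal approximation, one-sided | 77.6% | 77.7% |
| Two proportions, two-sided | 77.2% | 77.4% (0.7735) |

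The two-proportion result is the same for first-group rates from 5% to 90%, with the second rate set each time to give 80% power at 60 per group. Across all of these the loss is 2.3 to 2.8 points.

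**The case against.** The arithmetic in steps 2 to 4 is hard to dispute. The objections concern how much follows from it.

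- **Partial diaries.** Diaries are sent weekly (section 4.4.1), the outcome is a proportion of days, and section 4.7 does not restrict the analysis to completers. Someone who leaves on day 60 could supply about 60 days of data. This stands in part: if such data are used, less power is lost. But the plan has no rule for partial or missing diaries. Section 4.5 has participants leave the study for missed appointments or substantial non-compliance, and question 6 of Appendix H allows data to be excluded from the statistical analysis. Whether the data would be used is unresolved.
- **The 60 may be rounded or may already include losses.** It cannot be checked, because the effect behind it is undisclosed. But attrition is raised straight after the 60, so 60 evaluable is the natural reading. If 60 already allowed for losses, the 75 would have no stated basis.
- **The 25% may mean 15 added to 60.** The text describes loss over the study. Losing 15 of 75 is 20%, so the sentence would still need correcting.
- **The power statement may not describe the primary analysis.** It concerns the occurrence of symptoms, while section 4.7 makes the proportion of symptom-free days primary. This stands as a limit: the 77% carries over the plan's own claim and is not an independent power estimate for the primary outcome.

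A reader might also infer that the shortfall is larger because people in the same house share an allocation (section 4.4.3) and because participants can be removed after randomisation. The documents do not support adding these. They give no household count or within-house correlation, and clustering is a separate question from attrition. Removals are themselves exits and may already be within the 25%, so adding them could count them twice.

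**Conclusion.** The stated enrolment does not deliver the stated requirement under the plan's own attrition: about 56 per group remain, not 60. The 80% power claim then becomes about 77% (77.2% to 77.7%) for the same undisclosed effect. This rests on two assumptions: that 60 is the evaluable number giving 80% power, and that participants lost contribute no data. If partial diaries are analysed, the loss is smaller.

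A reader might go further and conclude that the trial is materially underpowered, or that its true power is known to be 77%. Neither is supported. The shortfall is about 4 participants per group and 2 to 3 power points, and absolute power cannot be verified without the effect size. The slip is certain as arithmetic, small in effect and cheap to correct.

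**What to change.** Keep 150 participants and restate the sentence in section 4.2.1. There are two ways.

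1. Preferred, because the plan gives a reason for its 25%: keep that rate and write, for example, *With 25% attrition about 56 participants per group are expected to remain, giving about 77% power for the effect that 60 per group would detect with 80% power, if participants lost contribute no data.*
2. Otherwise, state that 60 per group and 80% power hold only if attrition does not exceed 20%. This should be worded as a condition, since the plan offers no evidence that attrition will be that low. A reader might expect that keeping the diaries of people who stop the product or miss a visit would bring attrition close to 20%, but no figure in the documents supports that.

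Either way the cost is one sentence and a slightly less favourable figure, with no extra participants.

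Keeping both 25% and 80% would need 80 per group, 160 in total. That means 10 more participants and changes to sections 4.2, 4.2.1, 4.4.1 and 4.4.3 and the Budget. At the budgeted rates, travel, internet and diary come to 3 × 50 + 100 + 30 = R$280 per participant, or R$2,800 for 10, before products and copies.

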# **CONCOMITANT THERAPY**

If any participant takes concomitant drug therapy, as a necessity for the treatment of a medical condition, then the participant's maintenance during the experimental period of the study will be evaluated and defined at the discretion of the investigator. However, it is the investigator's responsibility to disqualify the entry of any individual who, during initial assessments, is using or consuming products that may hinder the interpretation of study results. All medications used by participants, on the day of inclusion, or at any time during the study period, will be recorded on the Visit Form (Appendix H). Participants may be given medications to treat adverse effects as necessary by the investigator or the participant's physician.

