# **APPENDIX E – INITIAL EXAM FORM**

**Number of participant: ___________ Age: ________Date: ____/____/____**

1. Is the participant between 18 years old and 70 years old? ( ) Yes No

2. Is the participant available to participate in the entire study? ( ) Yes No

3. Does the participant have good systemic health? ( ) Yes No

4. Is the participant willing to provide information related to their medical history?

( ) Yes ( ) No

1. Did the participant sign the informed consent form? ( ) Yes No

**If, for questions 1 to 5, there is a “no” answer, the participant is ineligible for the study. He should be dismissed, and question 14 should be completed. If the subject is eligible, complete questions 6-13.**

6. Is the participant participating in another clinical trial or has participated in a clinical trial in the last month? ( ) Yes ( ) No

7. Is the participant pregnant or breastfeeding? ( ) Yes ( ) No

8. Does the participant have a history of allergies to oral hygiene products, personal hygiene products, or their ingredients? ( ) Yes ( ) No

9. Does the participant currently have mouth irritation or use oral anesthetics?

( ) Yes ( ) No

10. Does the participant have diabetes? ( ) Yes ( ) No

11. Is the participant immunocompromised (HIV, AIDS, immunosuppressive drug therapy)? ( ) Yes ( ) No

12. Does the participant use complete dentures? ( ) Yes ( ) No

13. Does the participant have carpal tunnel syndrome or arthritis in the hands?

( ) Yes ( ) No

**If, for questions 6 to 13, there is a “yes” answer, the participant is ineligible for the study. He should be dismissed, and question 14 should be completed.**

14. Is the subject eligible to enter the study? ( ) Yes No ( )

Date: ________ Signature of the examining dentist: _______________________

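### No entry criterion addresses a current cold or ongoing respiratory symptoms and no symptom state is recorded before randomisation, so the primary outcome mixes new colds with pre-existing symptoms and loses power by an unknown amount

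*Combined protocol and SAP*

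**What the plan says.** The Aim is to assess the effect of gargling "on the incidence and duration of symptoms associated with flu and colds". Section 4.7 defines the endpoint: "The proportion of symptom-free days (i.e., none of the 10 symptoms were present) will be used for the primary outcome variable". Appendix F lists the ten items, among them runny nose, stuffy nose, sneeze, cough and tiredness. Each is scored 0 to 7, with no confirmation of cause.

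Four provisions bear on a candidate's symptoms at entry:

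- Section 4.2.2 requires "Good systemic general health as determined by study investigators". Appendix E question 3 repeats it: "Does the participant have good systemic health".
- The nearest exclusion in section 4.2.3 is "Have mouth irritation or use oral anesthetic sprays".
- Section 7 (Concomitant therapy) has the investigator disqualify anyone who at entry is "using or consuming products that may hinder the interpretation of study results".
- Appendix C has tick-boxes for asthma, breathing difficulties, lung problems and emphysema. No stated rule links them to eligibility, and rhinitis and sinusitis are not listed.

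None of questions 1 to 13 in Appendix E asks about a cold, flu or respiratory symptoms. Section 4.4.1 issues the symptom diary only once the initial assessments are done, and the list of initial-visit forms in section 5.3 has no symptom sheet. Section 4.7 has no baseline adjustment and no rule for symptoms already present at entry.

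**The concern.** A person with an untreated three-day-old cold, or with mild daily rhinitis, can satisfy every written criterion. The first starts follow-up with symptomatic days that began before any product use. The second may have few symptom-free days whatever the product does. Both enter the primary outcome on the same footing as someone who catches a new cold in week five.

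Participants whose outcome cannot respond dilute the mean difference. They also lie far from everyone else on the scale and so inflate the between-person variance. The trial plans on only 60 evaluable participants per group at 80% power. Without a pre-randomisation symptom value, the analysis cannot take that variance out afterwards.

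**Working it through.** **The plan's own figure.** Section 4.2.1 states 60 per group for 80% power, based on the sponsor's internal data. No rate, effect or SD is given, so the figure cannot be reproduced. For a two-sided 5% comparison of participant means (sidedness assumed), 60 per group corresponds to a standardised difference of (1.96 + 0.84) × √(2/60) = 0.51. I take that as the planned effect among entrants without chronic symptoms.

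**Chronic symptoms.** Every input here is an assumption. Let a share p of entrants be chronically symptomatic, with mean m symptom-free days, SD 5 points and no response to treatment. The others have mean 90% and SD s.

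- Mixture variance: V = (1−p)s² + p(0.05)² + p(1−p)(0.90−m)²
- Retained standardised effect: k = (1−p)s/√V
- Power = P(Z > 1.96 − 2.80k)

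Example with s = 0.12, m = 0.05, p = 0.05: V = 0.01368 + 0.00013 + 0.03432 = 0.0481, SD 0.219, k = 0.114/0.219 = 0.52, power 31%.

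| Case | p | SD (points) | k | Power |
|---|---|---|---|---|
| Harsher: s = 12, m = 5% | 2% | 16.8 | 0.70 | 50% |
| | 5% | 21.9 | 0.52 | 31% |
| | 10% | 28.0 | 0.39 | 19% |
| Milder: s = 18, m = 40% | 2% | 19.2 | 0.92 | 73% |
| | 5% | 20.7 | 0.83 | 64% |
| | 10% | 22.8 | 0.71 | 51% |

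A second set of assumptions (others: mean 80%, SD 20; chronic: mean 10%, SD 10) gives 57%, 43% and 27% power at 5%, 10% and 20% chronic. Dilution alone, with no added variance, gives 76%, 71% and 61% at the same shares. Most of the loss is therefore variance, which a baseline covariate can address.

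**What a baseline value could recover.** If it identified chronic participants perfectly, the third term of V would drop out. At p = 10% and s = 12, k = 0.108/√(0.01296 + 0.00025) = 0.94 and power is 75%. At p = 2%, k = 0.1176/√(0.01411 + 0.00005) = 0.99 and power is 79%. With s = 18 the results are the same to the nearest point. This is an upper bound, since one sheet classifies imperfectly.

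**Colds present at entry.** If a share q enters with d days of cold remaining, mean symptom-free days fall by q × d/90 in each arm. Lowest case: 0.05 × 5/90 = 0.3 points. Highest case: 0.15 × 10/90 = 1.7 points. With 10% and 7 days it is 0.8 points.

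**Validity.** In 20,000 simulated null trials with 60 per arm and 15% chronic participants in both arms, a participant-level t-test rejected in 5.1%. The simulation treats participants as independent. It does not cover a test on pooled days or shared households.

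**The case against.** Several stronger readings are tempting, and the documents do not support them.

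- *That nothing screens such people out.* The good-health criterion is judged by investigators, section 4.4.1 places the health questionnaire and clinical examination before the eligibility decision, and section 7 could catch someone taking cold or allergy medication. These filters exist. They are discretionary or act on products used, so untreated symptoms can pass.
- *That the trial cannot measure incidence.* The diary is dated and completed daily for 90 days, so new onset after a symptom-free interval can be derived. The plan simply does not define it. The aim also includes duration, so a cold present at entry that gargling shortens falls within it.
- *That the comparison is biased.* Background symptoms balance in expectation. Chance imbalance is already in the standard error of a participant-level test and should not be counted again beside the power loss.
- *That the Introduction describes a treatment population*, from "solution in the form gargling when flu and cold symptoms occur". The next sentence states the hypothesis as fewer occurrences of symptoms, so this reads as loose wording.
- *That advertising on social media will draw in people who are ill.* This is speculation. Section 4.4.1 relies mainly on invitation in the dental clinics.

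Two further objections carry weight. The internal data behind the 60 per group are not shown. If they came from an unselected population, the extra variance is already in the sample size and little or no power is lost. Keeping people with chronic rhinitis or cough is also a legitimate choice for a product already on the market.

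One might add that Appendix F looks back 24 hours, so the first sheet could serve as a baseline. The plan does not say when that sheet is completed, and does not require it before the participant knows which products were assigned.

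**Conclusion.** The concern holds in a limited form. The plan has no explicit criterion on a current cold or ongoing respiratory symptoms, no symptom record before randomisation, no baseline adjustment and no definition of new onset. The primary outcome is therefore a measure of symptom burden from any cause, and it does not isolate incident colds. A participant-level test stays valid. What suffers is power, precision and interpretation, above all of a null result.

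The size is unknown. With 2-10% chronically symptomatic entrants, the assumed cases give power of about 73-51% or 50-19% instead of 80%. These figures depend on the assumed means and SDs. At s = 18, the planned effect of 0.51 SD is about 9.2 points, nearly all the room above 90%, so the cases show a range and are not forecasts. Colds present at entry are the minor part. The missing criterion and baseline are certain from the text; the amount of power lost is not.

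**What to change.** 1. At the initial visit and before randomisation, have each candidate complete one Appendix F sheet, with an added question on the previous 7 days. List it among the initial-visit forms in section 5.3.
2. Add to section 4.2.3 and Appendix E that a candidate with a current acute respiratory infection is deferred and re-screened once symptom-free.
3. In section 4.7, compare the proportion of symptom-free days at participant level with the pre-randomisation symptom value as a covariate. As a supporting analysis, derive new-onset episodes after a defined symptom-free interval from the diary.
4. State whether the internal data behind the 60 per group came from people unselected for respiratory symptoms.

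Whether to exclude people with chronic rhinitis or cough is left to the sponsor as a choice of target population. The baseline covariate works either way. It addresses the added variance but not the dilution.

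The cost is one extra copy of an existing form at a visit that already takes place, one checklist question, a few sentences in section 4.7, and slightly slower recruitment while some candidates wait. The baseline has to be in place before enrolment, because it cannot be reconstructed reliably afterwards.
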